### Health economics

The health economic component will review quality and completeness of economic data generated by the trial itself (e.g. women’s self-report data on service contacts and quality of life outcomes, data from women’s maternity records) and data from external sources (e.g. unit cost data for costing service contacts and estimating intervention costs) necessary for conducting an economic evaluation in a future definitive trial. An assessment will also be undertaken of suitability of existing economic models that could support additional modelling of longer-term (out of trial) resource impacts and health outcomes linked to observed (within trial) impacts on weight loss as part of a definitive trial. This will identify whether or what additional evidence and modelling would need to be undertaken to support evaluation of longer-term costs and outcomes.

The health economic component will include primary analysis of economic data generated by the trial to gain preliminary insight into intervention cost-effectiveness. This will include the following:
Analysis of differences in overall costs between trial groups, including service contacts, clinical resource use, and weight management intervention costs. Sub-group effects on differences in costs between groups will be explored with specific reference to baseline BMI. This, with evidence on sub-group analysis of weight loss outcomes, will inform whether a definitive trial should be designed to evaluate variability in intervention cost-effectiveness between relevant sub-groups.A preliminary within trial cost-effectiveness analysis of the weight management intervention versus standard care using comparative feasibility trial data on resource use and costs and quality of life outcomes over a 12-month follow-up.

### Sample size calculation, selection, and loss to follow-up

A sample size of 190 women will allow a 30% loss to follow-up to ensure we achieve our required sample size of 130 women. This study is designed firstly to establish the rates at which women could be recruited and retained in a future definitive RCT and estimate critical parameters with necessary precision to inform sample size requirements. In particular, we require estimates of the standard deviation, and design effect for the primary endpoint, allowing for clustering by intervention group. One hundred thirty women will allow estimates of the required sample size for any given clinically important difference to within 30% of the true value.

Based on published data [17, 42] the mean (SD) percentage weight change following a Slimming World® (Alfreton, UK) programme of 12 weekly groups is − 5.5% (3.3). Assuming these numbers are typical, 65 women in each group (130 in all) would be required to detect a difference of 2% between active and control groups with 90% power. Of around 6600 women who give birth at the reference maternity unit over 12 months in 2017, 40% were overweight, 15% of whom were obese. Data on women with excessive GWG are not routinely collated. Potentially, 55 women booking each week would meet obese/overweight inclusion criteria. Recruiting 7–8 women each week over an 8-month (32 week) period would be sufficient to achieve the desired sample size to meet the aims of this feasibility study.

Compliance issues are an important consideration. Loss to follow-up among postnatal women can range from 30 to 40% [43, 44]. Experience of research in similar populations has shown that planned initiatives including flexible follow-up appointments, travel expenses, vouchers for returning questionnaires, and sending of reminders can reduce loss to follow-up. Follow-up appointments will be offered at weekends and week days, with the option to complete questionnaires at these appointments.

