### Trial feasibility objectives

The primary feasibility objective is to estimate the effect size for a likely primary study outcome in a future definitive trial, namely difference between study groups in weight change from booking to 12 months postbirth, expressed as percentage of weight change or weight loss in kilogrammes. Mean percentage change across all women gives greater power, and fewer women will need to be recruited. We will undertake pre-planned sub-group analysis of the primary assessment in women of different booking BMI categories. The primary endpoint for a future trial will be selected on grounds of power.

Other objectives include those most appropriate to support meeting the primary objective and inform progress to a definitive RCT. These will include rates of 5% and 10% weight reduction and changes in relation to aspects of healthy lifestyle and health behaviours, including diet and nutrition, breastfeeding, physical activity, smoking cessation, alcohol intake, self-esteem, and body image. Some included measures have been validated in relevant populations, including among women of reproductive age and women who have recently given birth.

Measures will be included in questionnaires at 6 and 12 months postnatally. Those marked with ‘**’ will also be included in the baseline questionnaire. Questionnaires will be ‘tailored’ for the intervention or standard care arm, to enable questions on uptake of support for weight management to be included at 6 and 12 months to inform trial process outcomes:
Dietary intake: The Dietary Instrument for Nutritional Education (DINE© University of Oxford)** [33]Soft drink intake: questions developed for the studyPhysical activity: The International Physical Activity Short-Form** [34]Mental health: Edinburgh Postnatal Depression Scale [35]Breastfeeding intent**, uptake, and duration, questions developed for studySleep patterns: questions developed for the studySmoking: smoking status/cigarette dependence** [36]Alcohol consumption: Alcohol Use Disorders Identification Test** [37]Self-esteem: Rosenberg Self-Esteem Scale** [38]Infant health: questions developed for studyImpact on body image [39]Resource utilisation and costs outcome measures: the EQ-5D-5L** and the Adult Service Use Schedule** [40]

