### Analysis

Process data will be analysed separately before examining relationships between quantitative and qualitative data, with synthesis completed in line with O’Cathain et al. [45]. Quantitative data will be entered onto the MedSciNet web-based data entry system. Retention and adherence will be considered from recruitment rate, consent rate, withdrawal and loss to follow-up (with reason), departures from randomised treatment, and prevalence of SAEs reported by treatment group and overall. Estimated differences and 95% confidence intervals will be calculated for specified primary and secondary analyses (significance at 5%). Sensitivity analyses will assess robustness of conclusions to missing outcome data and departures from randomised treatment. Analyses of potential efficacy will be based on the ITT sample, utilising follow-up data from all randomised women.

Differences between arms will be compared at 6 and 12 months postbirth adjusting for important prognostic factors (parity, maternal age, ethnicity, BMI at booking, and (as appropriate) baseline measurement). Data to inform process outcomes will be evaluated using descriptive analysis. Numbers (with percentages) will be presented for binary and categorical variables and means (standard deviations), or medians (with lower and upper quartiles) or geometric means for continuous variables will be presented. Stata version 15.1 or later will be used for analyses (StataCorp, College Station, TX).

Interviews will be recorded with women’s permission and transcribed and analysed using the framework method for thematic analysis [46]. Analyses will be deductively informed by the COM-B model for behaviour change [41]. Themes that emerge inductively will be captured, and efforts made to identify and explore disconfirming/outlier cases**.** Key topics and issues will be identified through familiarisation with transcripts by two researchers who will initially work independently and then together to discuss and agree the final coding framework with a third researcher. A series of thematic charts will be developed according to the coding framework, and data from each transcript summarised under each theme, enabling examination of similarities and differences of views within and between transcripts, and use of a constant comparative approach. Quantitative and qualitative data on acceptability of the intervention and other aspects of feasibility will be integrated using mixed-methods matrices [46].

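### The 90% power statement uses the SD of a 12-week programme and is not supported for the booking-to-12-month endpoint

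*Protocol article*

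**What the plan says.** The section on sample size gives two reasons for 130 analysed women.

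- **Precision.** The study is meant first to establish recruitment and retention rates and to estimate planning parameters, among them the SD and the design effect of the primary endpoint. The section says 130 women will place the required size of a future trial to within 30%.
- **Power.** Published data are cited for "the mean (SD) percentage weight change following a Slimming World® (Alfreton, UK) programme of 12 weekly groups", with values of −5.5% (3.3). The text continues: "Assuming these numbers are typical, 65 women in each group (130 in all) would be required to detect a difference of 2" per cent, with 90% power.

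The methods section on trial feasibility objectives makes estimating the effect size the primary feasibility objective. The outcome is the "difference between study groups in weight change from booking to 12 months postbirth", and Table 1 uses the same interval. The Analysis section states: "Analyses of potential efficacy will be based on the ITT sample, utilising follow-up data from all randomised women". It also specifies 95% confidence intervals with significance at 5%, and adjustment for parity, age, ethnicity, booking BMI and, as appropriate, the baseline measurement.

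**The concern.** The planning SD and the endpoint differ in four respects.

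| | Source of the 3.3 | Trial endpoint |
|---|---|---|
| Interval | 12 weekly groups | Pregnancy, birth and the following 12 months |
| Starting weight | Start of the programme | Antenatal booking |
| People | Those following the programme | All randomised women: controls, attenders and non-attenders |
| Population | Published programme data | Overweight and obese women, plus normal-BMI women selected for excessive gestational gain |

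The only link between the columns is the assumption that the published numbers are typical. The article does not argue that they carry over to the longer interval or to the control arm. Most of these differences would be expected to widen the spread.

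At stake is how a non-significant result is read. A published 90% power figure, attached to the primary feasibility objective and to testing at 5%, invites the conclusion that a 2-point effect has been ruled out. That conclusion could feed into the decision on a definitive trial.

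**Working it through.** **Inputs**

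- Difference 2 percentage points, power 90%, SD 3.3, 65 per arm: sample size section ("detect a difference of 2% between active and control groups with 90% power").
- Allocation 1:1: section on treatment allocation and randomisation.
- Alpha 5%: Analysis section. Two-sided testing is my assumption, from the pairing of 95% intervals with 5% significance.
- SD of change from booking to 12 months: not given. A range of 4 to 8 is assumed below.

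**1. Reproducing the plan's figure**

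n per arm = 2 (z₀.₉₇₅ + z₀.₉₀)² SD² / δ² = 2 × (1.960 + 1.282)² × 3.3² / 2² = 2 × 10.507 × 10.89 / 4 = 57.2, so 58. The t-test version gives 58.2, so 59. The stated figure is 65.

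Two unstated inputs would come close to it:

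- An SD of 3.5: 2 × 10.507 × 12.25 / 4 = 64.4, so 65.
- A design effect D in the intervention arm only, at SD 3.3: n = (1 + D) × 28.6, which equals 65 at D ≈ 1.27. At D = 1.2, power with 65 per arm is 90.9%.

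The text does not say whether either was used. The allowance for loss is in order: 130 / 0.7 = 186, and 190 × 0.7 = 133.

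**2. The margin**

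At SD 3.3 and 65 per arm, the standard error is 3.3 × √(2/65) = 0.579. Power is Φ(2/0.579 − 1.960) = 93.3%, or 92.9% by the t-test. The SD at which power is exactly 90% is 2 / [(1.960 + 1.282) × √(2/65)] = 3.52, about 7% above 3.3. Power reaches 80% at an SD of 4.07.

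**3. Power and precision over assumed SDs, 65 per arm**

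The half-width is t₀.₉₇₅,₁₂₈ × SD × √(2/65) = 1.979 × 0.1754 × SD = 0.347 × SD. The detectable difference uses the normal approximation.

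| SD (points) | Power for 2 points (t-test) | 95% CI half-width | Difference detectable with 90% power |
|---|---|---|---|
| 3.3 | 93% | 1.15 | 1.88 |
| 3.5 | 89.9% | 1.21 | 1.99 |
| 4 | 81% | 1.39 | 2.27 |
| 5 | 62% | 1.74 | 2.84 |
| 6 | 47% | 2.08 | 3.41 |
| 7 | 37% | 2.43 | 3.98 |
| 8 | 29% | 2.78 | 4.55 |

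**4. Do the article's own figures settle the SD?**

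They do not. The Introduction reports pooled results from a Cochrane review. Assuming equal arms and a simple interval, SD = (CI width / 3.92) × √n / 2:

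- Exercise, n = 53, −1.90 to 1.71 kg: 3.4 kg.
- Diet plus exercise, n = 573, −2.96 to −0.89 kg: 6.3 kg, inflated by any heterogeneity between trials.
- Diet, n = 45, −2.08 to −0.132 kg as printed: 1.7 kg. This interval is not centred on its mean of −1.70, so it may be misprinted.

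At an assumed body weight of 70 to 90 kg these are about 3.7–4.8%, 7.0–9.0% and 1.9–2.4%. They fall on both sides of 3.3%, and none covers booking to 12 months.

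Non-attendance alone could use up the margin. For illustration, suppose attenders lose 5.5% on average, non-attenders and controls average zero, and every group has SD 3.3. A 2-point difference then implies 2 / 5.5 = 36% attendance. The intervention-arm variance is 3.3² + 0.364 × 0.636 × 5.5² = 17.9 (SD 4.2). The pooled SD is √[(17.9 + 10.9) / 2] = 3.8, and power is about 85%.

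**5. The precision rationale**

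Required sample size is proportional to the variance. With 128 degrees of freedom, the 95% limits for the ratio of true to estimated variance are 0.79 and 1.30. The within-30% claim therefore reproduces, for independent normal data, and does not use the 3.3.

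**The case against.** The strongest reply is that the power sentence is openly conditional and comes second. The study is designed first for rates and planning parameters, the precision argument for 130 holds by itself, and the section headed Trial objectives says the aim is not to evaluate the intervention. The reported confidence intervals will show the precision actually achieved. All of this stands, and it limits the seriousness of the point. It does not remove it, because the stated condition does not say that the SD belongs to another interval and another population, and the methods still make the effect size the primary feasibility objective.

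The second reply is that covariate adjustment may recover power. It may, by an unknown amount. To bring the residual SD down to 3.52, the covariates would have to explain 1 − (3.52/SD)² of the variance: about 23% at an SD of 4, 50% at 5 and 66% at 6.

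The third reply is that 65 exceeds the 58 or 59 implied by the printed inputs, so some margin is built in. That is correct, but it covers an SD only up to about 3.5.

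A reader might go further and infer that the trial lacks 90% power, or could not detect a 2-point effect. The article does not support that. It gives no SD for this endpoint, the review figures point both ways, and even assumed SDs of 4 to 8 leave power between 81% and 29%.

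**Conclusion.** The point holds as a moderate correction to a stated design property. The 90% power claim is not supported for change from booking to 12 months, because its SD describes a 12-week programme and nothing in the article carries it across. Lower power is likely but not proven. The claim fails if the true SD, after any adjustment, exceeds 3.3 by about 7%. At SDs of 5 and 6 unadjusted power would be 62% and 47%. These figures assume a two-sided 5% test, 65 analysed per arm, equal SDs and no clustering. Separately, 65 does not follow from the printed inputs. Nor does it follow that 130 women are too few for the feasibility purpose, since the precision rationale reproduces without the 3.3.

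**What to change.** Revise the power paragraph of the sample size section:

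1. Withdraw the 90% power claim, or label it illustrative.
2. State that 3.3% is the SD of change following a 12-week programme, and that no SD for change from booking to 12 months was available.
3. Give the inputs that produced 65 per arm, including any rounding of the SD or any design effect.
4. Show power and 95% CI half-width over an assumed range of SDs. For 4 to 8, the half-width runs from about 1.4 to 2.8 points. Note that covariate adjustment may improve on these figures.
5. Rest the 130 on the existing precision argument.

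The cost is one paragraph and a less favourable stated power. Enrolment, conduct and analysis do not change.

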**Methods/analysis:**

Women will be recruited from one maternity unit in London. To be eligible, women will be overweight (BMI 25–29.9 kg/m^2^) or obese (BMI ≥ 30 kg/m^2^) as identified at their first antenatal contact, or have a normal BMI (18.5–24.9 kg/m^2^) at booking but gain excessive gestational weight as assessed at 36 weeks gestation. Women will be aged 18 and over, can speak and read English, expecting a single baby, and will not have accessed weight management groups in this pregnancy. Women will be randomly allocated to standard care plus lifestyle information and access to Slimming World® (Alfreton, UK) groups or standard care only. A sample of 130 women is required.

Feasibility trial objectives reflect those considered most important inform a decision about undertaking a definitive future trial. These include estimation of impact of lifestyle information and postnatal access to Slimming World® (Alfreton, UK) on maternal weight change between antenatal booking weight and weight at 12 months postbirth, recruitment rate and time to recruitment, retention rate, influence of lifestyle information and Slimming World® (Alfreton, UK) groups on weight management, diet, physical activity, breastfeeding, smoking cessation, alcohol intake, physical and mental health, infant health, and health-related quality of life 6 and 12 months postnatally. An embedded process evaluation will assess acceptability of study processes and procedures to women.

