### Treatment allocation and randomisation

Randomisation and allocation will be carried out by KCL’s Clinical Trials Unit web-based system. Women will be registered on the InferMed MACRO web-based data entry system by a research midwife prior to randomisation to allocate each a unique study number ‘PIN’. Research midwives will access the system and, using the PIN, initials, and date of birth, request randomisation. Unit of randomisation will be individual participant, allocated in a ratio of 1:1 to intervention and control. Selection bias will be minimised by ensuring all women eligible and recruited have equal opportunity of being allocated to each study group and follow-up completed, with information on women randomised and allocated but who opt out presented but clearly indicated as such. Use of intention to treat (ITT) analysis will limit attrition and analytical bias.

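### The 65 women per group said to be required for 90% power do not follow from the stated inputs: these need 58–59 per group, and 65 give about 93% power (minor, conservative)

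*Protocol article*

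**What the plan says.** The section on sample size, selection and loss to follow-up in the protocol article contains two separate arguments for the same number.

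- **Precision.** The trial is meant first to establish recruitment and retention rates and to estimate the SD and the design effect for the future primary endpoint. The section says that 130 women allow the sample size of a future trial to be estimated to within 30% of its true value.
- **Power.** From published data on a 12-week programme it takes a mean (SD) percentage weight change of minus "5.5% (3.3). Assuming these numbers are typical", and then concludes that "65 women in each group (130 in all) would be required to detect a difference of 2" per cent "between active and control groups with 90% power".

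The number 130 also appears in the Abstract ("A sample of 130 women is required"), at the start of the sample size section ("A sample size of 190 women will allow a 30% loss to follow-up to ensure we achieve our required sample size of 130 women"), and in Table 1 as the number to be retained to 12 months.

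**The concern.** The power sentence gives the difference, the SD and the power, and it presents 65 per group as what they require. All the ingredients for a two-sample comparison of means are in the article, so the figure can be checked directly, and it does not come out. The gap of 6–7 women per group is too large to be rounding.

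What is at stake is modest. A reader who checks the sentence cannot tell whether the power is misstated or whether an unreported input lies behind the 65 (a larger SD, a smaller difference, or some inflation of the variance). In a feasibility trial whose purpose is to inform a later sample size, the planning assumptions should be legible.

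**Working it through.** **Inputs**
- Difference δ = 2 percentage points, SD σ = 3.3 and power 90%: sample size section.
- Significance 5%: Analysis section, "specified primary and secondary analyses (significance at 5" per cent). Sidedness is not stated. Two-sided is inferred because the same sentence says "Estimated differences and 95% confidence intervals will be calculated".
- Allocation: "allocated in a ratio of 1:1 to intervention and control" (Treatment allocation and randomisation).
- Loss to follow-up of 30% is applied after the 130 (130/0.7 = 185.7, set at 190), so it is not part of the 65.
- Design effect: no value is given. It is listed as something the trial will estimate.

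**Step 1. Attempt to reproduce 65 per group**

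n per group = 2 × (z₀.₉₇₅ + z₀.₉₀)² × σ² / δ²
= 2 × (1.960 + 1.2816)² × 3.3² / 2²
= 2 × 10.507 × 10.89 / 4 = 57.2, so 58.

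The noncentral t calculation gives 58.2, so 59. The total is 116–118. The stated 65 (130 in all) is not reproduced.

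**Step 2. Power at 65 per group**

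δ / (σ√(2/65)) = 2 / (3.3 × 0.1754) = 3.455.
Normal approximation: Φ(3.455 − 1.960) = 0.933. Noncentral t: 0.929.

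The power is therefore about 93%, not 90%.

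**Step 3. Other readings of the stated inputs (n per group)**

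| Variant | n |
|---|---|
| One-sided 5% | 47 (normal), 48 (t) |
| Two-sided 2.5% | 68 |
| 80% power | 43 |
| 95% power | 71 |
| Rank test, efficiency 0.955 | 60–61 |
| Rank test, efficiency 0.864, or a 15% uplift | 66–68 |

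None gives 65, and the article names no rank test; it plans adjusted differences between arms.

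**Step 4. Unstated inputs that do give 65 at 90% power**
- SD of 3.52 (normal) or 3.49 (t), that is, about 3.5.
- Difference of 1.88 (normal) or 1.89 (t), that is, about 1.9.
- Variance inflation of 65/57.2 = 1.136 (normal) or 65/58.2 = 1.117 (t).
- A 10% allowance for loss on the t-based figure: 58.2/0.9 = 64.7. This would sit oddly with the separate 30%.

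The article does not say that any of these was used.

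**Step 5. Does 130 stand without the power sentence?**

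For a fixed difference and a fixed design effect, the required sample size is proportional to the variance. Reading the 30% as the upper 95% confidence limit of the variance ratio, df / χ²₀.₀₂₅(df), with the variance pooled over two groups:

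| Total n | df | Upper limit |
|---|---|---|
| 130 | 128 | 1.298 |
| 118 | 116 | 1.317 |
| 116 | 114 | 1.320 |

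The precision claim reproduces at 130 and would be missed at 116 or 118.

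**The case against.** The best defence is that nothing in the trial depends on this sentence. The precision argument comes first in the section, matches the stated purpose of the study, and supports 130 by itself. If the power sentence were deleted, 130, 190 and the Table 1 criterion would all remain. Moreover, 65 per group do detect a 2-point difference with at least 90% power, so only the claim that 65 are required is inexact. The difference detectable with 65 per group at 90% power is about 1.9, which rounds to the whole number in the text. Finally, an article condenses a fuller protocol, where a modest allowance might be documented.

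Most of this stands, and it sets the weight of the point. It does not remove the error. The article reports a difference, an SD, a power and a result, and the result does not follow from the rest. That is a misstatement in the text at hand rather than a detail left to another document.

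Two stronger readings are tempting and should be resisted.
- **That a smaller trial would do.** A reader might infer that 118 completers, or 118/0.7 = 169 recruits, would suffice. They would not: 118 misses the stated precision target (1.317 against 1.30).
- **That a clustering allowance may be counted twice, or omitted, in the definitive trial.** The section lists the SD and the design effect as quantities that this trial will estimate for that purpose. Nothing suggests that the 65 or the 130 would be reused there, so this harm is speculative.

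**Conclusion.** The power sentence is wrong as written, and the point is minor. On the stated inputs 90% power needs 58–59 women per group; the stated 65 is 6–7 higher, about 10–12%, and corresponds to about 93% power. The error is conservative: on these inputs the trial is not underpowered, and neither the recruitment target nor the retention criterion is affected.

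The conclusion assumes a two-sided 5% test, which the article implies but does not state; a one-sided test would widen the gap. It also assumes a simple comparison of two means with SD 3.3 in both groups and no design effect, since no value for one is given. The support for 130 rests on reading the 30% precision claim as an upper 95% confidence limit for the variance, a reading under which the claim reproduces.

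**What to change.** Replace the power sentence in one of two ways:
- *65 per group (130 in all) give about 93% power to detect a difference of 2% at SD 3.3, two-sided 5%*; or
- keep 90% power and state the additional input that was actually used, whether an SD of about 3.5, a difference of about 1.9%, or a named variance inflation.

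Either way, state that the test is two-sided, and keep 130 and 190 on the precision argument. The cost is one sentence, with no change to recruitment, follow-up or analysis.
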